## Abstract

**Background:**

Colorectal cancer screening participation is a preference-sensitive choice, in which trade-offs between benefits and harms must be made by individual citizens. Often the decision is made without any contact with healthcare professionals. Citizens with lower educational attainment tend to participate less in colorectal cancer screening than citizens with average educational attainment. Further, they tend to have lower levels of knowledge about colorectal cancer screening. Providing lower educational attainment citizens with a targeted decision aid embracing their diverse information needs might increase these citizens’ ability to make informed decisions. The aim of this trial is to test the effectiveness of such a newly developed self-administered decision aid.

**Methods:**

The LEAD (Lower Educational Attainment Decision aid) trial will be conducted as a two-arm randomized controlled trial among 10,000 50–74-year-old citizens, resident in the Central Denmark Region not yet invited to take up colorectal cancer screening. Citizens will receive a baseline questionnaire. Respondents will be allocated into the intervention or the control groups. Citizens in the intervention group will receive the decision aid whereas the control group will not. Those who return a stool sample within 45 days after receiving the screening invitation and those with medium or higher educational attainment are excluded. Both groups will receive a follow-up questionnaire 90 days after being invited to colorectal cancer screening.

A historic cohort consisting of 5000 50–74-year-old citizens resident in the Central Denmark Region, having received their screening invitation in the beginning of 2017 will be included. This cohort will receive a follow-up questionnaire 6–9 months after they received the screening invitation.

Informed choice will be evaluated by assessing levels of knowledge, attitudes, and screening uptake. Analyses will be conducted as intention-to-treat analyses. Additionally, differences between levels of worry and decisional conflict between groups will be assessed as secondary outcomes.

**Discussion:**

This trial will evaluate whether a targeted decision aid is a feasible way of enhancing informed choice among lower educational attainment citizens in colorectal cancer screening. Further, it may guide decisions about providing information material in cancer screening in general.

**Trial registration:**

ClinicalTrials.gov, NCT03253888. Registered on 17 August 2017.

**Electronic supplementary material:**

The online version of this article (10.1186/s13063-018-2921-z) contains supplementary material, which is available to authorized users.

## Background

Colorectal cancer (CRC) is a common cause of cancer-related deaths worldwide. In developed countries the age-standardized mortality rate of CRC is 14.7 and 9.3 per 100,000 men and women, respectively [1]. However, CRC mortality can be reduced by 25% in citizens undergoing screening with the guaiac fecal occult blood test (gFOBT) at least once [2]. The fecal immunochemical test (FIT) is superior to the gFOBT in detecting CRC and is now the preferred test [3].

Screening has obvious benefits, including reduced incidence of CRC, earlier stage diagnoses, and reduced mortality [2]. However, there are also adverse effects of screening, such as risk of over-diagnosis, unnecessary tests and complications to these, and psychological consequences. Hence, a decision to take up screening is preference-sensitive and includes a cognitive and emotional trade-off between benefits and harms, based on adequate information [4]. From an ethical standpoint, such a decision should be an informed decision.

In order to make an informed decision, comprehensible and easily accessible information is crucial. However, information material about CRC screening is often neither read nor understood by citizens with lower levels of health literacy [5]. Low health literacy is significantly associated with lower educational attainment [6]. In order to support informed decision making, decision aids have been developed to provide balanced information on healthcare [7]. Decision aids come in different formats (e.g. booklet, leaflet, online service, DVD, etc.) and they may encourage readers to reflect on the information in a structured way, for example by the means of “values clarification exercises” [8]. Studies have shown that decision aids can increase CRC knowledge and the proportion of citizens making an informed decision about screening uptake when used by citizens and healthcare professionals together [9, 10]. Furthermore, they can increase screening uptake [11–15]. However, the decision to take up CRC screening is often made without prior contact with healthcare professionals, and hence, decision aids need to be self-administered. Self-administered decision aids increase CRC knowledge [16–20] and informed choices made [18, 19], but may result in more negative screening attitudes [18, 19], while studies regarding screening uptake are inconclusive [16, 18–20].

In general, lower educational attainment citizens participate less in CRC screening compared with those who have average educational attainment [21, 22]. Further, they have higher CRC mortality compared to medium and higher educational attainment citizens [23, 24]. Tailoring a decision aid to this group could be advantageous, but their information needs are diverse, ranging from a desire for a clear recommendation to the need to know all the details [25]. Decision aids tailored to this group do exist [9, 10, 13], but are not self-administered [19], and none of them embrace diverse information and support needs. Hence, this research group has developed a decision aid tailored for lower educational attainment citizens [26]. It was designed as an online format, presenting information in steps, making it possible for citizens to get as much or as little information as they want, thereby embracing diverse information needs.

The aim of the LEAD (Lower Educational Attainment Decision aid) trial is to investigate the effectiveness of the newly developed decision aid tailored for lower educational attainment citizens on informed choice, as assessed based on knowledge of CRC and CRC screening, CRC screening uptake, and CRC screening attitudes. Further, the effectiveness on levels of CRC worries and decisional conflict will be assessed.

## Methods

### Setting

CRC screening with biennial FIT was introduced in Denmark in 2014 with an initial “prevalence round” of invitations for four years, where all citizens aged 50–74 years are invited once, according to month of birth. Citizens turning 50 or 75 years during the prevalence round are invited just before their birthday if not invited earlier. From 2018, all citizens in the target group will receive biennial invitations (identifying incident CRC). The screening program is locally administered in five regions. This study is carried out in the Central Denmark Region, which is the second largest region with roughly 395,000 citizens aged 50–74 years [27].

In the CRC screening program, the mailed screening invitation contains a screening kit (collection tube and collection paper), instructions on how to obtain the sample, an official information leaflet, and a pre-stamped, pre-addressed envelope. If a screening sample is not returned within 45 days, a digital reminder is sent (see below). Test results are digitally mailed to the citizens within one week after the test is received at the laboratory. Citizens with a negative test result are referred to the next screening round (two-year interval) and citizens with a positive test result receive an appointment for colonoscopy. Non-participating citizens are automatically referred to the next screening round.

Danish residents are obliged to order a digital signature which is used to log in to a secure national e-mail platform, where all mandatory digital communication with Danish authorities (including hospitals) takes place via the unique civil registration number. Some citizens (8.7% of the population aged 45–74 years during the summer of 2017 [28]) can be exempted from digital communication [29] and receive conventional mail via a remote printing system, in which an external supplier prints out and sends all letters to exempted citizens.

### Study design

The LEAD trial will be conducted as a two-armed, randomized controlled trial nested into the Danish CRC screening program in the Central Denmark Region. Included citizens will be randomly allocated to one of the following two study arms (Fig. 1):Screening reminder with the decision aid (intervention group);Screening reminder without decision aid (usual care/control group).

**Fig. 1 Fig1:**
[figure not shown]
Participant *flow chart*. Figure depicting the data collection, interventions, and participant flow in the trial

The intervention and control groups receive the baseline questionnaire before the screening invitation. This might increase screening awareness and possibly screening uptake and knowledge in these groups – a true Hawthorne effect. To be able to assess the effect of the questionnaire, a historic cohort will be introduced as in other decision aid trials [30]. This group will receive their questionnaire after screening invitation and uptake assessment.

This study entails evaluating the offer to use the decision aid. Even though participants may not necessarily use it, not using the decision aid is not a specific issue in this study as it is a pragmatic evaluation of offering it in a routine screening program.

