When citizens in the intervention group are due for a screening reminder, they will concurrently receive a separate mail containing a link for the decision aid. This strategy was chosen in order to avoid information overload, since other conventional information material is sent out along with the screening invitation. Further, first invitations are sent out by postal mail, and hence, the link is better provided in the reminders that are sent by digital mail.

Forty-five days after the citizens have received the intervention/screening reminder, they will receive the follow-up questionnaire. Reminder procedures for the follow-up questionnaire will be the same as for the baseline questionnaire. Citizens who do not return follow-up questionnaires within six weeks (i.e. going to the last page in the questionnaire and pressing submit) will be excluded from the study, since the consent to use data in the project will not have been given.

Citizens in the historic study arm will receive one questionnaire 6–8 months after being invited to participate in CRC screening. Reminder procedures for this questionnaire will be the same as for the previous questionnaires.

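### The historic cohort differs from arm 2 in more than the baseline questionnaire, so its contrasts should be exploratory and not part of the Table 1 hypotheses

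*Protocol article*

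**What the plan says.** The Study design section gives the purpose of the third group: "To be able to assess the effect of the questionnaire, a historic cohort will be introduced". The reason is that "The intervention and control groups receive the baseline questionnaire before the screening invitation", which might itself raise awareness, uptake and knowledge. Of the historic cohort it says "This group will receive their questionnaire after screening invitation and uptake assessment".

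The survey time of H is given twice, differently. The abstract says "This cohort will receive a follow-up questionnaire 6–9 months after they received the screening invitation"; Study processes says "Citizens in the historic study arm will receive one questionnaire 6–8 months after being invited to participate in CRC screening". For the randomized arms the abstract says "Both groups will receive a follow-up questionnaire 90 days after being invited to colorectal cancer screening".

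Table 1 gives 1 > 2 and 1 > H as the hypothesis for two primary elements, follow-up knowledge and uptake, and 1 < 2 and 1 < H for decisional conflict. It also lists worry at baseline as a comparison of 1, 2 and H. The regressions in Statistical methods use arm 2 as the reference for both arm 1 and H.

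**The concern.** A control for the questionnaire effect should differ from arm 2 only in not having received the baseline questionnaire. H differs in several other respects, and the article states no adjustment or limitation for them; its discussion of attrition bias covers only the randomized arms.

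Two consequences follow. First, a difference, or no difference, between arm 2 and H could be misread as the presence or absence of a Hawthorne effect. Second, a non-randomized contrast sits inside the primary hypotheses. If the two parts are read jointly, an aid that beats arm 2 could still miss the stated hypothesis because of who answered in H.

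**Working it through.** **1. Arm 2 and H side by side**

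| Feature | Arm 2 | H | Source |
|---|---|---|---|
| Entry | Answers and consents 7–20 weeks before invitation | First approached after uptake is assessed | Study processes; Study design |
| Expected response | 60%, then 80% at follow-up | 50% in one step | Power calculations |
| Outcome survey | About 90 days after invitation | 6–9 or 6–8 months | Abstract; Study processes |
| Invited | October–December 2017 | January–March 2017 | Study population |
| Age | 53–74 | 50–74 | Study population |
| Baseline questionnaire | Yes | No | Study design |

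Only the last row is the effect that H is meant to measure.

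**2. Expected numbers.** The article gives no figure for bias in H, so there is none to reproduce. Its planning rates imply:
- Total response in arm 2: 0.60 × 0.80 = 48%, against 50% in H.
- Analysed in arm 2: 5000 × 0.47 × 0.26 × 0.48 = 293.
- Analysed in H: 5000 × 0.47 × 0.26 × 0.50 = 305, assuming the day-45 exclusion also applies to H.

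Totals are similar, but the loss after the uptake decision is not: about 20% in arm 2 and 50% in H.

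**3. Uptake, illustration with no true difference.** The documents give no response rate by uptake status, so these are assumptions: true uptake p among day-45 non-returners of 20% or 30%; response in H of a among takers and b among non-takers. Observed uptake = p·a / (p·a + (1 − p)·b).

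- Mild, a = 0.60, b = 0.475: odds ratio (0.60/0.40)/(0.475/0.525) = 1.66.
- Strong, a = 0.65, b = 0.45: odds ratio (0.65/0.35)/(0.45/0.55) = 2.27.

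Arm 2 also loses follow-up non-respondents after the decision, so the same odds ratio is applied there, with a and b solved so that overall follow-up response is 80%.

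| True p | Odds ratio | H observed | Arm 2 observed | H minus arm 2 |
|---|---|---|---|---|
| 20% | 1.66 | 24.0% | 21.5% | 2.5 points |
| 20% | 2.27 | 26.5% | 22.2% | 4.3 points |
| 30% | 1.66 | 35.1% | 32.0% | 3.1 points |
| 30% | 2.27 | 38.2% | 33.0% | 5.2 points |

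First row: H = 0.20 × 0.60 / (0.12 + 0.38) = 0.240. Arm 2 has response 0.8585 in takers and 0.7854 in non-takers, so 0.20 × 0.8585 / 0.80 = 0.215.

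For scale, at an odds ratio of 2, with H response of 50%, the distortion is 3.5 points (p = 20%) or 4.5 points (p = 30%). With 293 against 305 analysed, a significant result in that direction has probability 17% or 21%, where 2.5% is nominal. An odds ratio of 1 gives no distortion, and one below 1 reverses the sign.

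**4. Knowledge, illustration.** Standard error of the difference in SD units: √(1/293 + 1/305) = 0.082. With no questionnaire or decision-aid effect, a drift of 0.1, 0.2 or 0.3 SD between about 3 months and the later survey would be significant at the two-sided 5% level with probability 23%, 69% or 96%. The drift itself is assumed.

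**5. Baseline worry.** H completes one questionnaire, months after invitation. The Setting section says that results are mailed within a week of the test reaching the laboratory and that a positive test leads to a colonoscopy appointment. Worry in screened members of H is therefore measured after the result, while arms 1 and 2 give theirs before the invitation.

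**6. Hypothesis against model.** 1 versus H combines the decision aid with the questionnaire. The planned regressions estimate 1 versus 2 and H versus 2; none is set up for 1 versus H.

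**The case against.** Surveying H after uptake is deliberate. A questionnaire before the decision would give H the very exposure it must lack. That stands, and it is why the point concerns the weight placed on H and not its existence. Likewise, H's lack of earlier contact with the knowledge items is no flaw in arm 2 versus H; it is part of the effect sought.

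Four stronger readings are tempting and are not supported.

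- A reader might infer that an ineffective aid could meet the primary hypothesis through H. The hypothesis is joint, 1 > 2 and 1 > H, so an ineffective aid should still fail the randomized part.
- A reader might infer that late surveying distorts uptake. Uptake comes from the screening database and is fixed at 90 days; only who responds and consents can affect it. That H uptake is limited to respondents is itself an inference from the 50% response assumption.
- A reader might apply response selection to H alone and arrive at 4 to 8 points. Arms 1 and 2 are filtered after the decision too: follow-up non-respondents "will be excluded from the study, since the consent to use data in the project will not have been given". Allowing for this gives the smaller net figures above.
- A reader might call the 1 > H results biased outright. If takers respond more readily, selection works against 1 > H for uptake; falling knowledge over time would work for it. Neither behaviour is documented here.

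**Conclusion.** The point holds in limited form. Arm 2 versus H cannot isolate the questionnaire effect, because recruitment point, survey time, invitation period and age range differ as well. The 1 > H parts of the primary knowledge and uptake hypotheses are open to bias of unknown size and direction. The net distortion of about 2.5 to 5 points in uptake rests on assumed response odds ratios of about 1.7 to 2.3, equal in both groups, and assumed true uptake of 20–30%; it is an illustration, not an estimate. 1 > H also mixes two effects and does not match the stated regressions.

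The baseline worry comparison with H is wrong as written, and the 6–8 and 6–9 month statements conflict. None of this touches the randomized comparison of arms 1 and 2.

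**What to change.** - In Table 1, remove the H part from the primary and secondary hypotheses, so that 1 versus 2 alone is confirmatory.
- Label all H contrasts exploratory. Restrict H to ages 53–74 and apply the same education and day-45 criteria as in the trial arms. State recruitment after uptake, later survey and earlier invitation period as limitations, and do not attribute the difference solely to the questionnaire.
- Delete H from the baseline worry row.
- Reconcile the 6–8 and 6–9 month survey windows.

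Aggregate uptake for everyone sampled into H would avoid selection by response, but should not be used unless it can be restricted to the same eligibility. Otherwise it mixes in early returners and citizens with more education, and education comes from Statistics Denmark, not from the screening database.

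The cost is a change of table and wording, a slightly smaller H sample, and a weaker claim about the Hawthorne effect.

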#### Study processes

Seven to 20 weeks before the invitation date, the included citizens in study arms 1 and 2 will receive a link to the baseline questionnaire via their digital mail (with remote printing for exempted citizens). Questionnaire reminders will be sent out after two weeks. Instead of a second questionnaire reminder, non-respondents will be contacted via telephone after four weeks and invited to fill out the questionnaire via telephone interview. In a pilot study, the response rates among lower educational attainment and medium/higher educational attainment citizens using an invitation and a two-week reminder were assessed at 27% and 55%, respectively. The response rates increased to 40% and 64%, respectively, in the two groups, by using telephone interviews. Accordingly, we expect telephone interviews to help reach more of the lower educational attainment citizens. Questionnaire respondents will also be asked for consent to the obtaining and analysis of screening data (date of invitation, reminder, receipt of test in laboratory, and test result) from the screening program database.

Citizens who respond to the questionnaire and give consent to the use of registry data will be randomly allocated into study arms 1 and 2. Allocation will be performed in the ratio 1:1 and will use a computer-generated algorithm for randomization, based on a simple randomization procedure. Randomization will be conducted based on the study participants’ record-ID numbers. Participants will not be able to change study arm after allocation and there will be no blinding.

Citizens who take up screening within 45 days after the screening invitation and citizens with medium or higher educational attainment (i.e. 10 years or more of education) will be excluded from the analyses after randomization. This might cause attrition bias. However, randomization will be conducted externally before screening uptake is known. Furthermore, educational attainment will not be available to researchers at an individual level, unless data are pseudonymized. However, educational level and screening uptake within 45 days of invitation is not expected to be associated with study arm and, hence, no attrition bias is expected.

When citizens in the intervention group are due for a screening reminder, they will concurrently receive a separate mail containing a link for the decision aid. This strategy was chosen in order to avoid information overload, since other conventional information material is sent out along with the screening invitation. Further, first invitations are sent out by postal mail, and hence, the link is better provided in the reminders that are sent by digital mail.

Forty-five days after the citizens have received the intervention/screening reminder, they will receive the follow-up questionnaire. Reminder procedures for the follow-up questionnaire will be the same as for the baseline questionnaire. Citizens who do not return follow-up questionnaires within six weeks (i.e. going to the last page in the questionnaire and pressing submit) will be excluded from the study, since the consent to use data in the project will not have been given.

Citizens in the historic study arm will receive one questionnaire 6–8 months after being invited to participate in CRC screening. Reminder procedures for this questionnaire will be the same as for the previous questionnaires.

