#### Primary outcome

Informed choice will be evaluated based on the following primary outcomes: consistency of knowledge about CRC screening, attitudes towards CRC screening, and screening uptake [34].

Knowledge will be measured via questionnaire before and after intervention using a seven-item scale developed by the authors based on both a literature search and patient information needs as previously clarified in focus group interviews [25]. Post-intervention levels and changes from baseline to follow-up will be evaluated.

Screening attitudes will be estimated using the translated four-item attitudes scale, ranging from 4 to 28 points [34]. The scale has been translated into Danish from English with conventional forward-backward translation [35]. Attitudes will be assessed at baseline and at follow-up.

Data on screening uptake will be collected from the CRC screening program database. Citizens will be defined as having taken up CRC screening if they return a stool sample within three months (90 days) after the screening invitation has been sent out [36].

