#### Questionnaires

Three different questionnaires will be administered in this trial: the baseline (knowledge, seven items; attitudes, four items [34]; worry, three items; health literacy – HLS-EU-Q16, 16 items [41, 44]) and follow-up (knowledge; attitudes; worry; decisional conflict, 16 items [37]) questionnaires, and the questionnaire for the historic study arm participants (knowledge; attitudes; worry; health literacy; decisional conflict) (Fig. 2).

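### With all blinding ruled out, callers who know the arm may collect follow-up knowledge and attitude answers by telephone; masking them would be cheap

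*Protocol article*

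**What the plan says.** The Study processes section of the protocol article closes its description of allocation with "Participants will not be able to change study arm after allocation and there will be no blinding". No exception is named for callers or anyone else who collects outcomes.

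The same section describes the baseline reminder scheme: a reminder after two weeks, and then "non-respondents will be contacted via telephone after four weeks and invited to fill out the questionnaire via telephone interview". For the post-intervention measurement it adds: "Reminder procedures for the follow-up questionnaire will be the same as for the baseline questionnaire". It also sets a limit: "Citizens who do not return follow-up questionnaires within six weeks" are excluded from the study.

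The Questionnaires section lists the content as "follow-up (knowledge; attitudes; worry; decisional conflict, 16 items [37]) questionnaires". Under Primary outcome, informed choice rests on "consistency of knowledge about CRC screening, attitudes towards CRC screening, and screening uptake". Uptake is taken from the screening programme database. Worry and decisional conflict are secondary outcomes.

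**The concern.** Participants cannot be blinded to being offered a decision aid. A person who telephones to read out a questionnaire has no need to know the arm, so this exposure is avoidable.

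There are two routes to bias:

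- **Measurement.** A caller who knows the arm may prompt, pause or accept a don't-know answer differently. The statistical methods score don't-know and missing knowledge answers as wrong, so a small prompt can change the score.
- **Selection.** Citizens who have not submitted within six weeks are dropped, so effort spent on calls partly decides who is analysed.

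At stake is the comparison of arms 1 and 2 on knowledge, where Table 1 states a direction in favour of arm 1, and on attitudes. A distortion introduced during the interview cannot be removed in the analysis.

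**Working it through.** **1. Does the telephone step fall after allocation?** Yes. The follow-up questionnaire goes out 45 days after the reminder or intervention, and the baseline reminder scheme applies to it. A call at four weeks lies inside the six-week return window, so telephone answers enter the analysis.

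**2. Which outcomes are exposed?**

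| Outcome | Status | Source | Exposed to caller |
|---|---|---|---|
| Knowledge | Primary element | Questionnaire | Yes |
| Attitudes | Primary element | Questionnaire | Yes |
| Uptake | Primary element | Screening database | No |
| Decisional conflict | Secondary | Questionnaire | Yes |
| Worry | Secondary | Questionnaire | Yes |

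**3. Does another safeguard cover this step?** Study processes names two: external randomization before uptake is known, and education not available to researchers at individual level. Both concern allocation and the post-randomization exclusions. Neither concerns follow-up interviewing.

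**4. How many answers might be collected by telephone?** For lower and medium/higher education, the pilot response "using an invitation and a two-week reminder were assessed at 27% and 55%, respectively". With telephone: "The response rates increased to 40% and 64%, respectively, in the two groups, by using telephone interviews".

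- Lower education: (40 − 27)/40 = 13/40 = 32.5% of responses came through the telephone step.
- Medium/higher education: (64 − 55)/64 = 9/64 = 14.1%.

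Expected analysed citizens per arm, from the rates under Power calculations (60% baseline response, 26% lower education, 47% with no sample by day 45, 80% follow-up response):

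- 5000 × 0.60 × 0.26 × 0.47 × 0.80 = 293.
- With the pilot's 40% baseline response in place of 60%: 5000 × 0.40 × 0.26 × 0.47 × 0.80 = 195.

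If the 32.5% share carries over:

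- 0.325 × 293 = 95 per arm.
- 0.325 × 195 = 63 per arm.

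As a lower alternative, also assumed, the 14.1% share gives 0.141 × 293 = 41 per arm.

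**5. How would a bias dilute?** Shift in the overall arm difference = telephone share × net between-arm bias among those interviewed. The document gives no figure for that bias. For scale only, with a 32.5% share:

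| Assumed net bias among interviewed (points) | Overall shift (points) | Share of the 14-point design difference |
|---|---|---|
| 10 | 3.3 | 23% |
| 20 | 6.5 | 46% |
| 30 | 9.8 | 70% |

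These rows show the mechanics and estimate nothing. The concern challenges no figure in the plan, and masking callers would not change the sample size.

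**The case against.** The strongest reply is that knowledge of the arm is inferred. The article does not say who makes the calls or what their lists show, and the no-blinding sentence sits beside a statement about participants and allocation. Call lists are the kind of detail an article may leave to a fuller document. This stands in part: a reader might infer that callers will know the arm, and the text does not support that. It does rule out blinding without exception, however, so it allows callers to know. That is a stated rule and not a mere omission.

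A reader might also infer that interviewer expectation and unequal call effort both push towards the hypothesis. The document does not support this. Expectation could favour arm 1 on knowledge. Extra calls in arm 1 could instead bring in more reluctant citizens who know less, which would lower that arm's mean. For attitudes Table 1 expects no difference, so there is no superiority direction to push. Nor does heavier telephone use among lower-education citizens create a difference between arms by itself.

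Other points that stand:

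- Knowledge items are multiple choice and each offers a don't-know option, which limits prompting without excluding it.
- Baseline answers precede randomization and cannot be affected.
- The pilot share may not transfer, because follow-up goes only to citizens who already answered at baseline, with 80% response targeted.

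The pragmatic aim of evaluating the offer of the aid explains why participants are unblinded. It gives no reason for callers to know the arm.

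**Conclusion.** The point holds as an avoidable route to bias of unknown size. The article rules out all blinding and uses telephone interviews for the post-allocation questionnaire, so callers who know the arm may collect two of the three primary elements and both questionnaire-based secondary outcomes. Uptake is unaffected.

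The exposure could reach about a third of the analysed citizens, roughly 63 to 95 per arm. That rests on the pilot telephone share holding among baseline respondents; a lower share gives fewer. The material does not show that bias will occur, how large it would be, or that call effort would favour arm 1. It supports a low-cost change to the stated rule and no claim that the primary comparison is invalid.

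**What to change.** In Study processes, replace the blanket no-blinding statement with wording to this effect: participants are not blinded; follow-up telephone callers receive call lists without allocation and read the questionnaire items verbatim. In addition:

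- record the mode of completion (online or telephone) for each follow-up questionnaire;
- record call attempts;
- compare telephone share and call attempts between arms 1 and 2.

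The cost is small: remove the arm from the call list and add a mode field and a count of attempts. If the people who send the decision aid link also make the calls, those tasks would have to be separated; the article does not say whether they are the same people. The main limit is that some citizens may reveal their arm during the call. The article says that use of the decision aid will be measured but not how. If it is asked in the call, those items should follow the outcome scales. Coding the arms for the analyst is an optional extra and not part of this point. The change needs to be in place before follow-up calls begin.
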